#### Primary outcome measures

Self-management is measured by using the revised Summary of Diabetes Self-Care Activities measure (SDSCA) [35]. The revised SDSCA contains 11 items, measuring six separate domains: general diet (2 items), specific diet (2 items), exercise behaviours (2 items), glucose monitoring (2 items), foot care (2 items) and smoking (1 item). Ten items are rated on an eight -point Likert scale, measuring the number of days a certain self-care behaviour is performed during the last week (0–7 days). The 11^th^ item measures smoking (yes/no) and the number of cigarettes smoked. Each of the domains is measured separately. The revised SDSCA shows an adequate internal consistency and test-retest reliability and is sensitive to change. The measure has been validated against other measures of diet and exercise [35].

Diabetes-specific health-related quality of life is assessed by the Problem Areas in Diabetes scale (PAID) [36], measuring diabetes-related emotional distress. The PAID consists of 20 items on a five -point Likert scale, ranging from 0 (not a problem) to 4 (a serious problem). Scores are transformed into a 0–100 scale for interpretation, with higher scores indicating greater diabetes-related emotional distress. The PAID has a strong concurrent and discriminant validity [37], has been proven to be responsive to change [38] and has been validated for Dutch T2DM patients [36,37].

#### Secondary outcome measures

Cognitive and emotional illness perceptions are assessed with the IPQ-R [28]. The first section of the IPQ-R measures different symptoms experienced by patients and whether they believe these symptoms are caused by their diabetes (identity scale; 14 items). The second section of the IPQ-R consists of seven subscales, measuring ‘time-line acute/chronic’ (6 items); ‘time-line cyclical’ (4 items); ‘consequences’ (6 items); ‘personal control’ (6 items); ‘treatment control’ (5 items); ‘coherence’ (understanding of T2DM, 5 items) and ‘emotional representation’ (6 items). In the third section, patients’ causal believes (18 items) are measured. The ‘identity scale’ is measured dichotomously (yes/no). All other items are measured on a five-point Likert scale ranging from 1 (strongly disagree) to 5 (strongly agree). The subscales of the IPQ-R have a good internal consistency and an acceptable test-retest stability [28].

Attitudes towards diabetes are measured with the Diabetes Attitude Scale (DAS-3) [39]. The DAS-3 consists of five subscales, measuring perceived seriousness (7 items); psychosocial impact (6 items); patient autonomy (8 items); value of tight control (7 items) and need for special training (5 items). The items are measured on a five-point Likert scale ranging from 1 (strongly disagree) to 5 (strongly agree). The DAS-3 is considered a reliable and valid general measure of diabetes-related attitudes across different groups of patients and health care professionals [39].

Patients’ perceptions of partner support are assessed by using a questionnaire developed by Buunk, Sanderman, and Nieuwland [40], which measures three different dimensions of partner support; active engagement (5 items); protective buffering (8 items) and overprotection (6 items). The items are measured on a five-point Likert scale ranging from 1 (never) to 5 (always). The three subscales have a moderate to good internal consistency [40].

Patient empowerment is assessed by the Dutch Diabetes Empowerment Scale (Dutch DES-20) [41]. The questionnaire consists of five subscales, assessing dissatisfaction and goal achievement (6 items), coping and motivation (4 items), obtaining support (3 items), overcoming barriers (4 items) and determining suitable methods (3 items) in a five-point Likert scale, ranging from 1 (totally disagree) to 5 (totally agree). The Dutch DES-20 was found to be a reliable and valid instrument [41].

### Sample size

The sample size calculation is based on detecting a clinically relevant change on the PAID, as a result of the programme. Since there is no consensus on the minimal important difference (MID) on the PAID, we decided to set the MID at half a standard deviation (SD); a commonly used solution when scores have no direct interpretation and no clinical results exist to determine a relevant percentage [42]. In Dutch T2DM patients, the SD found on the PAID was 20, with a mean score of 22.5 points (scale 0–100) [36]. To establish a 10-point difference with the power set at 80% and the α at .05 (two-sided), 63 patients are needed in each condition (intervention/control). However, taking the clustering of patients within groups into account, an oversampling of 15% is needed to conduct multi-level analyses. When accounting for an additional drop-out of 10%, 2 × 80 patients will have to be recruited.

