##### Pilot

The course was pilot-tested on feasibility and acceptability in November and December 2011. Sixteen T2DM patients and eight partners from a general practice in the region of Utrecht participated in the pilot-study (attrition rate 21.6%). During the pilot, all course sessions were led by a health psychologist in order to evaluate whether the correct psychological models and techniques were used. During the first session, a practice nurse was also present to provide medical information on T2DM. Feasibility and acceptability of the course were explored by means of an evaluation form at the end of the course and by feedback of the participants during the course sessions. Based on the evaluation of the pilot, the manual was adapted and a screening questionnaire was developed for the RCT to ensure that only T2DM patients who experience some degree of difficulties or uncertainties will participate.

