The current study also poses a number of challenges and drawbacks. We foresee a few potential threats to reliability and generalisability of the study. First, a selection of participating patients in the study is expected, as a result of a selective non-response of patients of older age and patients from the non-western origin. Consequently, specific target groups might be missed and generalisability of the results of this study limited. Furthermore, a possible selection bias might also be found among the GPs in the study. Participating GPs will probably represent a group more open to research and innovation and may also be more motivated to improve diabetes care. Consequently, their patients might already receive various educational or support programmes which may negatively impact on participation willingness. In order to keep non-response and drop-out rates as low as possible, personalised invitation letters from GPs and reminders to initial non-responders will be sent. Furthermore, the course sessions and information meetings will be organised in easily accessible locations in the area of the participating patients and GPs. Finally, a practical challenge is also foreseen in the group-based format of the course. In spite of the fact that group-based sessions pose many advantages, they are more difficult to organise and cannot be completely adapted to individuals needs and preferences (e.g. time, location, topics discussed), which may result in increased (selective) drop-out. Furthermore, we emphasise the importance of creating and keeping a positive and stimulating group climate during the course sessions. Dominant and/or negative group members can negatively influence the group climate and interactions, and consequently, the effectiveness of the programme. Therefore, we will recruit diabetes nurses and practice nurses who already have experience in leading group-based courses and extra attention will be paid on how to deal with dominant group members during the training.

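### The 10% drop-out allowance has no stated source and is not reconciled with the pilot's 21.6% attrition; if the pilot rate carried over to outcome data, power would be about 74% to 77% instead of 80%

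*Protocol article*

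**What the plan says.** The Sample size section of the protocol article builds the target on the PAID. The inputs are "To establish a 10-point difference", an SD taken from Dutch patients ("the SD found on the PAID was 20"), "with the power set at 80"% and "the α at .05 (two-sided"), from which "63 patients are needed in each condition (intervention/control"). That number is raised by 15% for clustering within course groups, and then: "When accounting for an additional drop-out of 10"%, which brings it to 2 × 80. No source is given for the 10%.

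The Pilot section reports that sixteen patients and eight partners from one general practice "participated in the pilot-study (attrition rate 21.6"%). The pilot ran in November and December 2011.

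The Discussion says of the difficulty of fitting group sessions to individual needs: "which may result in increased (selective) drop-out". It also lists measures to limit loss: personalised letters, reminders to initial non-responders and easily accessible locations.

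**The concern.** The only observed attrition rate in the article is about twice the planned one (21.6 / 10 = 2.2), and it comes from the course under test. The trial also follows patients for longer than the pilot's two months: three monthly sessions, a booster three months later, and T2 six months after T1. The article names a reason why drop-out may rise, yet it neither explains the 10% nor says why the pilot rate should not apply.

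The 10% fixes the recruitment target. If true loss is nearer the pilot rate, the trial has less than its stated power for the PAID, a primary outcome, at the difference chosen as minimally important. A null result could then be read as stronger evidence against a relevant effect than it is.

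**Working it through.** **Inputs.** From Sample size: difference 10, SD 20, two-sided α 0.05, power 80%, clustering allowance 15% (used below as a divisor of 1.15), drop-out 10%, 80 recruited per arm. From Pilot: attrition 21.6%.

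**Reproducing the plan's figure.** n per arm = 2 × (1.96 + 0.8416)² / (10/20)² = 62.8, so 63. Then 63 × 1.15 = 72.45, and an allowance for 10% loss brings this to about 80. The plan's number reproduces.

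**Power of 80 per arm.** Effective number per arm m = 80 × (1 − loss) / 1.15. Power = Φ(10/SE − 1.96), with SE = 20 × √(1/m₁ + 1/m₂).

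| Loss | m₁, m₂ | SE | 10/SE | Power |
|---|---|---|---|---|
| 10% both arms | 62.6, 62.6 | 3.575 | 2.798 | 79.9% |
| 15% both arms | 59.1, 59.1 | 3.678 | 2.719 | 77.6% |
| 20% both arms | 55.7, 55.7 | 3.791 | 2.638 | 75.1% |
| 21.6% intervention, 10% control | 54.5, 62.6 | 3.704 | 2.699 | 77.0% |
| 21.6% both arms | 54.5, 54.5 | 3.830 | 2.611 | 74.2% |

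The first row shows that the plan has no slack. For scale, keeping 80% by recruitment alone at 21.6% loss in both arms would need 63 × 1.15 / 0.784 = 92.4, so 93 per arm.

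**What the T0 score does to this.** The article gives no correlation ρ between T0 and follow-up PAID, so 0.4 to 0.6 is an assumption. Adjusting for T0 multiplies the outcome variance by (1 − ρ²). Comparing raw change scores multiplies it by 2(1 − ρ). With 21.6% loss in both arms (54.5 effective per arm):

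| ρ | T0-adjusted: equivalent m | Power | Raw change score: equivalent m | Power |
|---|---|---|---|---|
| 0.4 | 54.5/0.84 = 64.9 | 81% | 54.5/1.2 = 45.4 | 66% |
| 0.5 | 54.5/0.75 = 72.7 | 85% | 54.5/1.0 = 54.5 | 74% |
| 0.6 | 54.5/0.64 = 85.2 | 90% | 54.5/0.8 = 68.2 | 83% |

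The choice between these two analyses moves power by more than the drop-out question does.

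**How firm is the 21.6%?** No whole number of losses gives it from the pilot counts. If 16 was the starting number, 3/16 = 18.8% and 4/16 = 25.0%; if 24, 5/24 = 20.8% and 6/24 = 25.0%. If 16 was the number remaining, 4/20 = 20.0% and 5/21 = 23.8%; if 24, 6/30 = 20.0% and 7/31 = 22.6%. With 16 patients, the exact 95% interval for 3 losses is 4% to 46%, and for 4 losses 7% to 52%. Both include 10%.

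**The case against.** The strongest reply is that the two rates may not measure the same thing. The 10% concerns patients lost to the outcome analysis. The 21.6% is attrition in a feasibility pilot judged by an evaluation form and participant feedback, and it may count leaving the course, or include partners. Under the intention-to-treat principle in the Statistical analysis section, a patient who leaves the course but returns the questionnaires is not lost. This stands, and so does the imprecision shown above: the pilot does not refute 10%.

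Three further points carry weight.

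- After the pilot the manual was adapted and a screener added, and the Discussion plans steps to limit drop-out. The article does not say how far these should lower attrition.
- The pilot tested the multi-session course, whereas controls attend one meeting. Nothing in the article supports 21.6% in the control arm, which is why 77.0% belongs beside 74.2%.
- The planned three-level model uses T0, T1 and T2, so baseline already enters and partly observed patients contribute. This does not by itself restore the power. The Abstract says that change scores are compared, and at ρ = 0.5 a raw change score gains nothing over an unadjusted comparison.

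A reader might infer that the sample size contains an arithmetic error, or that 2 × 80 simply gives 74% power. The article supports neither. Its calculation reproduces from its stated inputs, and the 74% requires the pilot rate to hold in both arms, for outcome data, in an unadjusted analysis.

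**Conclusion.** The point holds as a conditional shortfall from an unreconciled input. The article plans for 10% loss without a source, reports 21.6% from its own pilot, says that the group format may increase drop-out, and does not connect the three. At 10% loss the stated power is right (79.9%) but has no margin. If the pilot rate applied to outcome data, power would be about 77% with the higher loss in the intervention arm only, or about 74% with it in both arms. These figures assume an unadjusted comparison and the plan's own 15% clustering allowance.

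The deficit is therefore between 0 and about 6 percentage points over the article's own range of attrition. That is of moderate weight and is not a must-fix: the pilot evidence is weak, and a T0-adjusted analysis would more than make up the difference over the assumed correlations.

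**What to change.** Make two changes.

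1. In Sample size, reconcile the 10% with the pilot's 21.6%. State what the pilot figure counted and out of how many, and why the trial should lose fewer patients from the outcome analysis. Then give the power of 2 × 80 as a range, about 74% to 80% over 10% to 21.6% loss for an unadjusted comparison.
2. In Statistical analysis, specify that the PAID comparison adjusts for the T0 score and does not compare raw change scores, and align the Abstract. State the T0–follow-up correlation assumed. At 0.4 to 0.6, power at 21.6% loss in both arms is about 81% to 90%.

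The cost is a rewritten sample size paragraph and a sentence on the model. No extra patients are needed. The stated power becomes slightly less favourable only if the adjustment is not adopted.

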### Statistical analysis

The study is a two-arm randomised controlled trial with repeated measures over time and continuous outcome variables. Descriptive statistics (mean values and frequencies) will be calculated to evaluate the scores on primary and secondary outcome measures on T0, T1 and T2 separately. The effectiveness of the programme will be analysed by a three-level multilevel model: groups, patients and measurements (T0, T1, and T2). This type of analysis allows us to both test the main effectiveness of the condition, its effectiveness over time, as well as the interaction effects of condition (intervention/control) × time. By including groups as a separate level in the analysis, possible effects of the different regions, course leaders and group climate are corrected for. Data will be analysed according to the intention-to-treat principle. All analyses will be performed using MLwiN.

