**Methods/Design:**

We aim to recruit 160 recently diagnosed T2DM patients and their partners from general practices in six different regions in the Netherlands. Patients need to be diagnosed with T2DM for one to three years and have to experience some degree of diabetes-related difficulties, as measured with a three-item screener. Participating patients and their partners are randomly allocated to the intervention or control condition. Participants in the intervention condition receive three monthly group sessions and a booster session three months later. Participants in the control condition receive a single information meeting. Data will be collected at baseline (T0), directly after the programme (T1) and six months post-programme (T2), including: self-management, diabetes-specific health-related quality of life, illness perceptions, attitudes, social support and empowerment. A three-level multilevel model will be used to compare change-scores between the conditions (intervention/control) on each outcome.

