### Aims and hypotheses

The primary aim of this study is to test the effectiveness of the ‘Living with diabetes’ course on enhancing self-management behaviours and diabetes-specific health-related quality of life in T2DM patients (one to three years post- diagnosis), compared to an attention control condition.

It is hypothesised that participation of T2DM patients in the group-based self-management support programme will result in:

a) Enhanced self-management and diabetes-specific health-related quality of life directly after the programme and at six months post-programme, as compared to an attention control condition.

Furthermore, we hypothesise that participation in the group-based self-management support programme will result in patients:

b) Holding more adaptive illness perceptions and attitudes towards T2DM;

c) Experiencing more activating partner support;

d) Feeling more empowered to manage their condition

Directly after the programme and at six months post-programme, as compared to an attention control condition.

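### The main effect of condition over T0–T2 does not estimate the programme effect, and the change-score contrast uses the baseline less efficiently than adjustment would

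*Protocol article*

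**What the plan says.** The Statistical analysis section specifies "a three-level multilevel model: groups, patients and measurements (T0, T1, and T2"), so baseline is one of the response occasions. It says this model makes it possible to "both test the main effectiveness of the condition, its effectiveness over time, as well as the interaction effects of condition (intervention/control) × time". It does not say which of these terms decides effectiveness.

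The Methods/Design paragraph of the abstract describes the same analysis as follows: "A three-level multilevel model will be used to compare change-scores between the conditions (intervention/control) on each outcome".

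The Aims and hypotheses section asks for a benefit "directly after the programme and at six months post-programme, as compared to an attention control condition". The quantities of interest are therefore the arm differences at T1 and at T2.

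The Sample size section takes "the SD found on the PAID was 20, with a mean score of 22.5 points (scale 0–100") as its input and concludes: "To establish a 10-point difference with the power set at 80% and the α at .05 (two-sided), 63 patients are needed in each condition". It then adds 15% for clustering and 10% for drop-out.

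**The concern.** Patients are randomised individually, so the expected arm difference at T0 is zero. A condition term that covers T0 as well as the follow-ups mixes an occasion on which no effect can exist with two on which it can. Depending on what else is in the model, the term is either a diluted effect or no treatment effect at all. Yet it is listed first among the tests of effectiveness.

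The other two statements, condition × time and change scores, do target the programme effect. They use T0 by subtracting it in full, which is the most efficient use only when follow-up tracks baseline almost perfectly. At lower correlation, subtraction adds noise that regression adjustment would avoid.

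Two things are at stake. The main-effect test could miss a real effect, or disagree with the interaction and leave the reader unsure which to believe. And power available from data already collected would go unused.

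**Working it through.** **Inputs from the Sample size section:** difference δ = 10 PAID points, SD = 20, two-sided α = 0.05, power 80%, 63 per condition before inflation.

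**Assumptions:** the documents give no correlation between occasions, so a common r is varied from 0.3 to 0.8. SDs are equal at T0, T1 and T2, and the effect is 10 points at both follow-ups. Clustering is left out; the 63 is the article's own figure before its clustering allowance.

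**1. The plan's own figure.** n = 2 × (20/10)² × (1.96 + 0.8416)² = 62.8, so 63 per arm, with power 80.1%. Then 63 × 1.15 = 72.45. Multiplying by 1.1 gives 79.7 and dividing by 0.9 gives 80.5. The stated 63 and 2 × 80 reproduce, apart from rounding.

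**2. Main effect without the interaction.** The expected coefficient is (0 + 10 + 10)/3 = 6.67 points. The SD of a patient's three-occasion mean is 20·√((1 + 2r)/3).

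**3. Change from T0 to one follow-up.** The target is 10 points and the SD is 20·√(2(1 − r)).

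**4. One follow-up adjusted for T0.** The target is 10 points and the SD is 20·√(1 − r²). The variance of (3) divided by that of (4) is 2(1 − r)/(1 − r²) = 2/(1 + r).

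Power is Φ(target/SD × √(63/2) − 1.96). For example, at r = 0.3 the change score has SD 23.66, and 10/23.66 × 5.612 − 1.96 = 0.41, which gives 66%.

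| r | Main effect, T0–T2 | Change score, one follow-up | Baseline-adjusted, one follow-up | Variance ratio 2/(1 + r) |
|---|---|---|---|---|
| 0.3 | 72.6% | 66.0% | 83.7% | 1.54 |
| 0.4 | 67.6% | 72.6% | 86.5% | 1.43 |
| 0.5 | 63.0% | 80.1% | 90.0% | 1.33 |
| 0.6 | 58.9% | 88.1% | 93.9% | 1.25 |
| 0.7 | 55.2% | 95.2% | 97.6% | 1.18 |
| 0.8 | 52.0% | 99.3% | 99.7% | 1.11 |

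For 80% power the main effect would need 76 per arm at r = 0.3, 95 at 0.5 and 114 at 0.7. The change score at one follow-up would need 88, 63 and 38. The baseline-adjusted contrast would need 58, 48 and 33.

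**5. Both follow-ups averaged.** The change of the T1–T2 mean from T0 has SD 20·√(1.5(1 − r)). Its power is 78.2% at r = 0.3, 84.1% at 0.4 and 90.0% at 0.5. Averaging therefore removes most or all of the change score's shortfall against 80%. Adjustment gains from averaging too, so the advantage of adjusting for T0 does not vanish.

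**6. What each coefficient is.** This was checked on one simulated complete data set (126 patients, r = 0.6, true effect −10 at T1 and T2):
- With the interaction in the model and T0 as reference, the condition coefficient was 0.78, equal to the raw T0 difference.
- The condition × time coefficients were −9.246 at T1 and −11.505 at T2, identical to the arm differences in change from T0.
- Without the interaction, the condition coefficient was −6.133, equal to the arm difference averaged over the three occasions: 0.784 + (−9.246 − 11.505)/3.

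**The case against.** The strongest reply is that the plan does not rest on the main effect. The same sentence lists condition × time, which carries the programme effect when T0 is a response. The wording says what the model allows, not which term decides. This stands: a reader might infer that the trial's conclusion hangs on a test biased towards no effect, and the text does not support that.

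A reader might also infer that the abstract and the Statistical analysis section conflict. They do not. In complete data the abstract's change-score comparison is the condition × time contrast, as step 6 shows. It differs only from the main effect.

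Nor is T0 as a response an error in itself. A model that constrains the T0 means to be equal across arms keeps T0 as a response and is about as efficient as covariate adjustment. The article does not describe its coding.

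Under randomisation the change score is unbiased, so the issue there is efficiency alone. The threshold of r = 0.5 for 80% power applies only to a single follow-up and to an assumed correlation.

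It is also tempting to call the SD of 20 a mistake. It is not: 63 per arm reproduces, the change-score SD equals 20 at r = 0.5, and sizing on the raw SD is conservative for a baseline-adjusted analysis.

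Finally, this is a condensed article, and its full protocol or analysis plan may name the deciding contrast. That absence is not the point here. The point concerns two things the article does state: a main effect offered as a test of effectiveness, and a comparison of change scores.

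**Conclusion.** The point holds as a free improvement, not as an error that must be fixed. As a test of effectiveness, the main effect of condition over T0–T2 does not answer the hypotheses. It targets two thirds of a constant effect (6.7 of 10 points), with power below the planned 80% at every r examined, or it is only the baseline difference. That dilution does not depend on r; the power figures do.

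The condition × time or change-score contrast is valid. Its cost against baseline adjustment is a variance ratio of 2/(1 + r) at one follow-up, which is 18 percentage points of power at r = 0.3, 10 at r = 0.5 and less than 1 at r = 0.8. These figures assume equal SDs and correlations, complete data, no clustering and the article's 63 per arm.

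**What to change.** In the Statistical analysis section, remove the main effect of condition over T0–T2 from the tests of effectiveness. Name as the programme effect the condition differences at T1 and at T2 adjusted for baseline. Either model T1 and T2 as responses with T0 as a covariate, or keep T0 as a response and constrain its mean to be equal in both arms. Replace the change-score wording in the abstract with the same statement.

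The cost is a few sentences of text. T0 is already collected, the multilevel structure and software can stay as they are, and the sample size needs no change.

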### Allocation to conditions

After obtaining the signed informed consent form, patients will be randomly allocated to the intervention or control condition. Randomisation will be conducted electronically by a researcher who is not involved in the study.

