#### Intervention

Participants allocated to the intervention group are invited to take part in the group-based self-management support programme, together with their partner. Patients who do not have a partner, are instructed to bring a close friend or relative instead. Each course group consists of six to ten patients, accompanied by their partner (or close friend/relative). The course consists of three two-hour monthly meetings and one follow-up meeting (‘booster session’) after three months. The group sessions are led by two trained diabetes nurses or practice nurses and are delivered in medical and community centers in the different regions.

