#### Attention control condition

Participants in the attention control condition are invited to a single 1.5 – hour information meeting, together with their partner (or close friend/relative). During this meeting, patients and their partners receive medical information about diabetes (e.g. causes, complications, treatment) from a professor in general practice and diabetes care. The information meeting serves as an attention control condition to control for the attention paid to being diagnosed with T2DM when participating in this study. Hence, the information that patients and partners receive during the information meeting is provided according to the classical didactic method; i.e. providing information that is important from a medical point of view, but not tailored to the specific and more comprehensive needs of the patients.

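### As described, the group level does not enter the standard error of condition × time, because course leaders and group climate act only after T0; the abstract's change-score wording would avoid this, and the two descriptions conflict

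*Protocol article*

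**What the plan says.** The Statistical analysis section says that effectiveness "will be analysed by a three-level multilevel model: groups, patients and measurements (T0, T1, and T2". T0 is therefore one of the responses and not a covariate. The terms to be tested are the main effect of condition, its effect over time, "as well as the interaction effects of condition (intervention/control) × time". The section then credits the group level with a specific correction: "By including groups as a separate level in the analysis, possible effects of the different regions, course leaders and group climate are corrected for". It names no group effect that changes over time.

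The abstract (Methods/Design) describes the analysis differently: "A three-level multilevel model will be used to compare change-scores between the conditions (intervention/control) on each outcome".

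Four other places bear on the point:

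- Allocation to conditions: "After obtaining the signed informed consent form, patients will be randomly allocated to the intervention or control condition".
- Intervention: "Each course group consists of six to ten patients, accompanied by their partner (or close friend/relative". Each group has two nurses, three meetings and a booster.
- Attention control condition: controls come to one 1.5-hour meeting, where they "receive medical information about diabetes (e.g. causes, complications, treatment) from a professor in general practice and diabetes care".
- Discussion: "Dominant and/or negative group members can negatively influence the group climate and interactions, and consequently, the effectiveness of the programme".

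**The concern.** At T0 no course has been held, so a nurse pair or a difficult group member cannot have affected the baseline score. Such effects appear at T1 and T2 and are by nature group differences in change. The Discussion expects exactly this, since it says that group climate can alter how well the programme works.

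A group intercept that is equal at T0, T1 and T2 describes something else: groups that differ by the same amount throughout. It subtracts out of any change from baseline, and so out of condition × time, which is the term that carries the programme effect. If this is the model fitted, the interval for the programme effect omits the clustering for which the Sample size section enlarged the trial by 15%. The larger sample protects power. It does not protect the error rate if the standard error leaves that variance out.

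The arms' groups also differ in kind: small courses that meet repeatedly with nurse pairs, against a didactic information meeting. One undifferentiated group variance would be a doubtful fit.

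**Working it through.** **Inputs from the documents.** SD of the diabetes-distress scale (PAID) 20, difference 10, two-sided α 0.05, power 80%, 15% for clustering and 10% for dropout (Sample size); groups of 6 to 10, midpoint 8 (Intervention).

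**Assumptions.** The article gives neither an ICC nor a correlation over time. I take the correlation r as 0.5 to 0.7. I define the ICC as the variance of the post-T0 group effect divided by 20² = 400. I use 9 groups of 8 per arm, that is 72 patients (80 less 10%). The number and size of the control meetings are not stated, so I show two cases: controls cluster like the courses, or not at all.

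**1. The plan's own figure.** n = 2 × (1.96 + 0.842)² × 20²/10² = 62.8, so 63 per arm. Then 63 × 1.15 = 72.45, and 72.45/0.9 = 80.5 (or 72.45 × 1.1 = 79.7). This agrees with 80 per arm. With a design effect of 1.15 = 1 + (m − 1) × ICC, the implied ICC is 0.15/(m − 1): 0.030, 0.021 and 0.017 for groups of 6, 8 and 10.

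**2. The group intercept cancels.** Write a score as fixed part + group intercept + patient intercept + residual. In T2 − T0 both intercepts subtract out and only residuals remain. At r = 0.6 the residual variance is 400 × 0.4 = 160 and the variance of change is 320. The standard error of condition × T2 is √(2 × 320/72) = 2.981. Generalised least squares gives 2.981 for group-intercept variances of 0, 8.56 and 20 alike. A REML fit to one simulated data set gave 2.933 without the group level and 2.933 with it.

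**3. What the standard error should be.** If a group effect with variance s² arises after T0 in both arms, each arm's mean change gains s²/9:

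- s² = 8.56 (ICC 0.021): √(8.889 + 2 × 8.56/9) = √10.791 = 3.285
- s² = 20 (ICC 0.05): √(8.889 + 2 × 20/9) = √13.333 = 3.651

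**4. Type I error.** In units of SD², let c = 2(1 − r). A course group's mean change has true variance ICC + c/8. An analysis with no group variance in change takes it as (ICC + c)/8. With R the ratio of true to assumed variance of the arm difference, the type I error is 2[1 − Φ(1.96/√R)]. For r = 0.6 and ICC 0.021, both arms clustering: R = 0.1214/0.1027 = 1.182, giving 7.1%. With only the course arm clustering: R = (0.1214 + 0.1)/(0.1027 + 0.1) = 1.092, giving 6.1%.

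| ICC | r | Both arms cluster | Course arm only |
|---|---|---|---|
| 0.021 | 0.5 | 6.7% | 5.9% |
| 0.021 | 0.6 | 7.1% | 6.1% |
| 0.021 | 0.7 | 7.9% | 6.4% |
| 0.05 | 0.5 | 9.0% | 7.0% |
| 0.05 | 0.6 | 9.9% | 7.5% |
| 0.05 | 0.7 | 11.4% | 8.3% |

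A null simulation of the three-occasion model (6,000 runs per setting, r = 0.6) agrees. With both arms clustering and with the course arm only, it gave 7.0% and 6.2% at ICC 0.021, and 10.8% and 8.2% at ICC 0.05. With no group effect it gave 5.7% and 5.0%. Comparing group-mean changes instead gave 4.1% to 5.3% at these two ICCs.

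**The case against.** The strongest reply is that the article lists levels, not a random-effects structure. It does not use the word intercept and does not exclude a group-by-time coefficient. Such detail commonly sits in a full protocol or analysis plan, and the abstract's change-score wording points to a model in which the problem does not occur. This stands in part. The article does not prove that an intercept-only model will be fitted. It does affirm a definite correction and credit it to the group level alone, in a model with T0 among the responses. On that description the correction does not reach the programme effect. That the abstract implies another model is a reason to reconcile the two.

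It can also be said that the group level enlarges the standard error of the main effect of condition. It does: the baseline contrast goes from 3.33 to 3.57 and 3.87 at group-intercept variances of 8.56 and 20. With T0 among the responses, however, that term is a baseline difference or a time average diluted by T0, not the programme effect.

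A reader might infer several stronger points that the documents do not support:

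- **Region is left uncorrected.** Stable regional differences are absorbed by a group intercept and cancel from change anyway. Region as a fixed effect is a modelling preference.
- **The error rate is grossly inflated.** That needs an ICC well above the roughly 0.02 that the 15% allowance implies.
- **Both arms are given one common group variance.** The article does not say so.
- **Estimation method, degrees of freedom and handling of never-attenders are missing.** These are ordinary analysis-plan content, and their absence from an article is no fault.

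**Conclusion.** The point holds for the model as the Statistical analysis section describes it: the stated correction for course leaders and group climate does not reach condition × time. The abstract and that section describe analyses with different standard errors.

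The consequence is moderate. The type I error is about 6–8% at the ICC implied by the plan's allowance, and about 8–10% at an assumed ICC of 0.05 with correlation 0.6. These figures rest on the assumed ICC and correlation, on groups of 8, and on whether control meetings induce clustering. The cancellation is exact only with complete balanced data. That leader and climate effects start after baseline is inferred from T0 preceding the programme, because the flow figure is not available.

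The sample-size arithmetic is not at fault. The point does not show that the trial's conclusion would be invalid, and it falls away if the full plan already places the group effect on follow-up or on change.

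**What to change.** State one model in both the abstract and the Statistical analysis section, with the group random effect acting after baseline. Any of three forms will do:

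- T1 and T2 as responses with T0 as covariate, and groups as the top level;
- change scores from T0 as responses, as the abstract already suggests, with groups as the top level;
- T0, T1 and T2 as responses, with a group random coefficient on an indicator for occasions after T0.

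Let the group variance differ between course groups and control information meetings. Limit the sentence on correction to leader and climate effects under that model.

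This is a change of wording and model specification before analysis; it needs no new data and no change of design. The price is a slightly wider interval for the programme effect. At the implied ICC and r = 0.6 it is about 4.5% wider if only the courses cluster (√1.092 = 1.045) and about 9% wider if both arms do (√1.182 = 1.087).
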